#### Secondary outcomes

In the RCT, the change in EEG metrics between post and pre stimulation of each session will be estimated and will stand as our secondary outcome. More specifically, analyses will focus on changes in whole brain connectivity markers as well as on power spectrum for each frequency band and brain response complexity. The alpha-band participation coefficient will be used to determine the response of a patient to the stimulation in the crossover stimulation protocol by means of pre and post stimulation differences. The same metrics will be computed and compared for the longitudinal trial before and after the 4 weeks treatment period. Additionally, for the latter study, TMS-EEG derived PCI will be computed and compared using the same method. TMS-EEG data will be analyzed with EEGLAB,^1^ FieldTrip,^2^ Brainstorm,^3^ MNE-Python^4^ and in-house MATLAB (SSP BioMedical Data Analysis Package; SiSyPhus Project; Version 2.5e) and Python scripts. The resting state data will be analyzed with a dedicated analysis pipeline (35). Continuous EEG resting state data will be filtered between 0.5 and 45 Hz and segmented into 10 s epochs. Then, data will be thresholded to remove clear-cut artifacts. EOG and ECG will be used to inform the removal of artifactual data epochs. An independent component analysis (ICA) will be used to remove remaining artefactual components from the EEG signal. Data will be used to compute spectral connectivity in the frontal and parietal areas in the delta, theta and alpha frequencies and expressed in graph theorem-based metrics (e.g., participation coefficient in the alpha band). Further, a set of these graph-theoretic parameters will be extracted from the network analyses and used to train and test a machine-learning model. We will analyze the parameters’ capacity to inform and predict treatment outcome independently (univariate regressions) and combined (multivariate pattern analysis and machine learning).

Data analysis will be carried out using RStudio (57). Analyses will be based on means ± standard deviations (SDs) for normally distributed quantitative variables, and as median and interquartile range (P25 – P75) for the skewed distributed variables. Numeric outcomes (e.g., the number of responders to the 4 weeks rTMS programme) will be summarized using count and proportion (%). Results will be considered significant at the 5% critical level (*p* < 0.05) and will be corrected using Holm correction for multiple comparisons. The Cohen’s d effect size will be calculated from the difference in means and standard deviations between baseline and post-treatment comparing active with sham interventions.

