**Discussion:**

This study seeks to identify which brain region (front or back) is best to stimulate for the treatment of patients with DoC using rTMS, and to characterize the neural correlates of its action regarding recovery of consciousness and functional outcome. In addition, we will define the responders’ profile based on patients’ characteristics and functional impairments; and develop biomarkers of responsiveness using EEG analysis according to the clinical responsiveness to the treatment.

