Eligibility will be derived from medical records and clinical visits. Inclusion criteria will be the following: patients with DoC due to acquired brain injury classified according to international guidelines as UWS/*VS* or MCS with at least two repeated behavioral assessments with the CRS-R within 10 days prior to inclusion; ≥ 18 years old; > 28 days post-injury; and stable vital parameters. As for exclusion criteria, they will be the following: no previous neurological deficits prior to the brain lesions; no pregnancy; no contraindication for TMS (e.g., uncontrolled epilepsy, that is, seizure within 4 weeks prior to enrollment, metallic implant in the skull, pacemaker, craniotomy under the stimulated site, peri-ventricular shunting device, sensitive skin); no sedative drugs or drugs thought to interfere with brain stimulation such as Na or Ca channel blockers (e.g., carbamazepine) or NMDA receptor antagonists (e.g., dextromethorphan); no drugs or substances which have strong potential of seizure induction (imipramine, amitriptyline, doxepine, nortriptyline, maprotiline, chlorpromazine, clozapine, foscarnet, ganciclovir, ritonavir, phencyclidine, ketamine, gamma-hydroxybutyrate, alcohol, and theophylline); and no current enrollment in other therapeutic clinical trial for the whole duration of the treatment protocol and follow-up. Patients will still receive all the standard medical and para-medical care from their facilities such as sensory stimulation or physical therapy. Table 1 summarizes all inclusion and exclusion criteria. In the present study, we will not exclude patients with lesions at the stimulation site (i.e., over the DLPFC or the AG) as it will enable us to document if patients with this structural profile show a lower rate of clinical responders compared to patients with healthy brain tissue at the target location.

**Table 1 tab1:** Study inclusion and exclusion criteria.

Inclusion criteria	Exclusion criteria
Age ≥ 18 years old	Previous neurological deficits prior to the brain lesions
Acquired cerebral damage of known etiology	Pregnancy
Diagnosed in UWS/*VS* or MCS as defined by at least two CRS-R assessments performed during the screening period Time since injury >28 days	Contra-indication for TMS (e.g., uncontrolled epilepsy, that is, seizure within 4 weeks prior to enrollment, metallic implant in the skull, pacemaker, craniotomy under the stimulated site, implanted brain device)

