#### Personalized parallel trial

This trial will include three arms (i.e., DLPFC rTMS, AG rTMS and the sham-controlled condition). After a 1 week washout period following the randomized crossover study, the personalized parallel trial will be conducted. Based on their behavioral (primary) or electrophysiological (secondary) responses to either the left DLPFC or left AG treatment in the crossover RCT, patients will be assigned to one of two groups (i.e., DLPFC group if the patient was a responder to the DLPFC stimulation; AG group if the patient was a responder to the AG stimulation). If no behavioral response nor EEG change from the RCT could be obtained regarding the best stimulation hotspot or if the patient is a responder to both sites, the patient will be randomized into one of the two stimulation hotspots in a 1:1 ratio. Then, all patients will be randomized between the experimental condition and the sham condition following a 2:1 ratio by a randomized order generator. Only the investigator in charge of the randomization will be aware of the patients’ group allocation. The assigned intervention (i.e., active stimulation versus sham stimulation) will be concealed from the patient, the family, the care providers and all investigators involved in the patient’s assessment for the whole duration of the treatment phase. The evaluator will stay blind from the sequence as well as from the stimulation group during treatment and follow-up. Moreover, analyses will be conducted in a triple blind fashion (see *rTMS device* point for more information about blinding methods). All patients included in the trial will undergo 4 weeks (i.e., 20 working days) of stimulation. Behavioral effects will be assessed with the CRS-R at baseline and once a week during the 4 weeks stimulation protocol. Fifteen minutes of high-density EEG resting state will be performed right before and right after the first session as well as before and after the last session. Eventually, TMS-EEG acquisitions will be performed the first and last day of the 4 weeks protocol. As we will assess the effects following a single session (first stimulation session) and after 4 weeks of rTMS, we will be able to compare the effect of a single versus repeated sessions of stimulation. Figure 3 depicts an overview of the two studies.

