#### EEG

High-density resting state EEG will be recorded using a BrainVision device (BrainAmp, BrainProducts, GmbH, Gilching, Germany). EEG signals will be measured in microvolts, sampled at 500 Hz and referenced to the vertex (Cz) using 64-channels TMS-compatible EEG nets. During the 15 min of recordings in Study 1 and 2, patients will be kept awake (e.g., eyes open) by the experimenter. EEG signals are sensitive to movements and DoC patients are often unable to comply with the instruction to stay still during the recordings. Therefore, in case of agitation or heavy artifacts, recording times will be adapted to obtain enough data to perform the analyses. The resting state data will be used to obtain spectral power and brain connectivity using the graph theory, which have proven to correlate with behavioral recovery of patients with DoC (35).

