### Power calculation

There are currently no RCTs available in the literature simultaneously testing the effects of DLPFC and AG rTMS in patients with DoC. As no clear-cut information could be drawn from the literature, a dedicated power analysis was done using G*Power software (56). Assuming a medium effect size of *f* = 0.5 at an alpha error level of 0.05 and a power of 0.8 with ANOVA or multiple regression analysis, 74 patients need to be recruited to detect meaningful differences in the primary outcome (CRS-R) between the real versus sham stimulation groups. Considering a 20% dropout ratio, the number of patients to be recruited adds up to 90.

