### Data analysis

#### Primary outcomes

For both crossover and longitudinal trials, primary analyses will focus on the detection of behavioral changes (i.e., enhanced behavioral total scores and/or changes in the level of consciousness as defined by the CRS-R) at the group level, comparing the sham interventions to the active interventions; and at the individual level, comparing post treatment to pre-treatment data. Along the same lines, analyses will also offer a comparison of the effects of frontal and parietal active rTMS on patients’ behavioral scores following one session of stimulation for the crossover RCT, and 4 weeks of stimulation for the longitudinal trial. Behavioral CRS-R total scores and subsequent index scores (50) will be defined as our primary outcome. Group treatment effects will be assessed with calculation of the difference between each group post-treatment and pre-treatment score means. Furthermore, we will identify clinical responders to (1) a single session of rTMS in the crossover trial and (2) the 4 weeks treatment protocol of the longitudinal trial as patients who will display new sign(s) of consciousness following treatment that was not present at baseline nor during the screening phase. In that context, further subgroup analyses will also be conducted along age, etiology, time since injury and diagnosis at inclusion.

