### Dissemination of results

Results of this clinical trial will be published in peer-reviewed open-access journals as original research articles and will be presented at various scientific conferences. The first publication will cover the clinical (CRS-R) and electrophysiological (connectivity markers) results of the RCT. The second publication is planned to report the clinical (CRS-R) and electrophysiological (connectivity markers and PCI) results of the personalized clinical trial and the follow-up period. A third publication is reserved for a detailed description of the machine-learning classifier developed to determine the features of treatment responders.

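### Univariate regressions and a classifier on a response defined without sham cannot tell EEG markers of general recovery from markers of benefit from rTMS, chiefly in the 4-week parallel trial

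*Protocol article*

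**What the plan says.** - **Method.** Under Secondary outcomes, graph-theoretic EEG parameters train and test a machine-learning model. Their capacity is then examined to "inform and predict treatment outcome independently (univariate regressions) and combined (multivariate pattern analysis and machine learning").
- **Response.** Under Primary outcomes, clinical responders are "patients who will display new sign(s) of consciousness following treatment that was not present at baseline nor during the screening phase". Study objectives and hypotheses gives the same kind of definition. Neither refers to what happens under sham.
- **Purpose.** The abstract's Discussion paragraph promises to "develop biomarkers of responsiveness using EEG analysis according to the clinical responsiveness to the treatment". Dissemination of results reserves a third paper for the "machine-learning classifier developed to determine the features of treatment responders". The main Discussion hopes for a phenotype linked to the effectiveness of stimulation.
- **What is known of the markers.** The EEG section describes spectral power and graph-based connectivity as measures "which have proven to correlate with behavioral recovery of patients with DoC".
- **Control data.** In the parallel trial, "all patients will be randomized between the experimental condition and the sham condition following a 2:1 ratio". In the crossover each patient has one sham session at each site.
- **Where sham is used.** The article compares active with sham for the group-level CRS-R effect and for Cohen's d. It names no such comparison for the predictor models.

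**The concern.** Whether a marker predicts response to rTMS is a question about the active-minus-sham effect: does that effect change with the marker? The matching null hypothesis is no marker-by-arm interaction. A regression of outcome on the marker alone has a different null, namely that the marker is unrelated to outcome. A marker that follows recovery to the same extent under active and sham breaks the second null and leaves the first intact.

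The article itself makes that situation likely. It says the metrics track behavioral recovery. Patients may enter "> 28 days post-injury", so some are subacute, and treatment lasts four weeks. Its introduction also cites a randomized trial of 20 Hz stimulation in which every group improved, sham included. Some recovery without active stimulation is therefore to be expected.

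At stake is whether the responder profile and the third publication answer their own question. Without a sham reference they could describe who improves anyway and present it as who benefits from rTMS.

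**Working it through.** **The plan's own figures.** The article gives no figure for the predictor analysis. The only sample size is under Power calculation: 74 evaluable and 90 recruited, "at an alpha error level of 0.05 and a power of 0.8". I take 74 as given. It does not reproduce from the stated f = 0.5 (34 for a two-group ANOVA, 42 for three groups), but that is a separate matter and nothing below depends on it.

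**Inputs**
- N = 74, from Power calculation. Allocation 2:1, from Personalized parallel trial: 74 × 2/3 ≈ 49 active and 25 sham.
- Two-sided 5% test. The article gives 0.05 without stating sidedness.
- r, the correlation of marker with CRS-R change, equal in both arms. **Assumption**: the article gives no value, so 0.2, 0.3 and 0.4 are shown.
- Main effect of active stimulation: 0 or 0.5 SD (assumption). The result hardly depends on it.

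**Model.** Outcome = r × marker + √(1 − r²) × noise + main effect × arm. There is no interaction, so the marker is purely prognostic and every claim that it predicts benefit is false. 5,000 simulated trials per setting.

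**How often the tested term is significant, N = 74**

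| Analysis | r = 0.2 | r = 0.3 | r = 0.4 |
|---|---|---|---|
| Univariate, active only | 28% | 56–57% | about 83% |
| Univariate, all patients | 39–40% | 72–74% | 94–95% |
| Marker plus arm main effect (marker term) | 39–40% | 74% | 95% |
| Univariate, all patients, at 0.05/10 | about 13% | 39–41% | 75–78% |
| Marker-by-arm interaction | about 5% | about 5% | about 5% |

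Across r from 0 to 0.5 and N of 74 or 90, the interaction test rejects in 4.5–5.4% of runs. With r = 0 every model stays near its nominal level.

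**Hand check by Fisher's z.** Rejection ≈ Φ(√(N − 3) × atanh(r) − 1.96).
- All patients, r = 0.3: 8.426 × 0.3095 = 2.608; Φ(0.648) ≈ 74%.
- Active only, r = 0.3: √46 × 0.3095 = 6.782 × 0.3095 = 2.099; Φ(0.139) ≈ 56%.
- All patients, r = 0.3, at 0.05/10 (critical value 2.807): Φ(2.608 − 2.807) = Φ(−0.199) ≈ 42%.

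These agree with the simulation to within about a percentage point.

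**What the table shows**
- Restricting to active patients does not help. The lower rates reflect only the smaller sample.
- An arm main effect does not help. It shifts the arm means and leaves the marker slope as it was.
- Holm lowers the rates but does not cure the fault, because the wrong null is being tested. The 0.05/10 row assumes a family of ten markers; the article does not define the family.

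**Power of the right test.** For a marker related to outcome only under active stimulation, simulated interaction power is about 57% at N = 74 and 64% at N = 90 when r = 0.5 versus 0, and about 23% and 27% when r = 0.3 versus 0. By hand at N = 74, the standard error of the difference in Fisher's z is √(1/46 + 1/22) = 0.259. Then 0.5493/0.259 ≈ 2.12 gives Φ(0.16) ≈ 56%, and 0.3095/0.259 ≈ 1.19 gives Φ(−0.77) ≈ 22%.

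**The case against.** **The model terms are inferred.** The sentence contrasts parameters taken singly with parameters taken together. It lists no covariates and does not say which patients enter or whether the outcome is sham-referenced. A condensed article may leave this to an analysis plan that is not shown. This stands in part: a reader should not take it as established that the final models omit arm. But the article does name a method, a univariate regression has one predictor, and the only definition of response it gives has no sham reference. An unseen plan would have to depart from the published wording to repair this.

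**A false claim is not certain.** A reader might infer that a prognostic marker will always be declared a predictor. The article does not support that. The rate depends wholly on an assumed r, and Holm correction is planned. The article also does not say whether the cited correlation with recovery is concurrent or prospective.

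**The crossover differs.** It is tempting to apply the same rates there. Nothing in the article supports carrying a correlation with recovery over to the CRS-R change around one 20-minute session, where spontaneous recovery should be small. This stands, and no rates are claimed for the crossover.

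**The consequence is limited.** One might infer that patients would be selected for rTMS, or refused it, on such a marker. The article plans a publication and says nothing of such use.

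**Overlap.** The sham-free responder definition is part of the same root. Changing it would largely repair the crossover. The parallel trial has no active-minus-sham difference per patient, so there the interaction is still needed.

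**Conclusion.** The concern holds for the 4-week parallel trial, and in weaker form for the crossover. As described, the predictor analysis tests association with outcome, while its results are presented as features of response to treatment. No other part of the article closes that gap. In the parallel trial a purely prognostic marker can, and often would, be reported as predictive.

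The size of the problem, 28–95% uncorrected over both analysis sets and 13–78% pooled at the assumed Holm step, rests on r between 0.2 and 0.4, a linear marker–outcome relation, 74 evaluable patients and 2:1 allocation. The direction does not rest on the particular r: any non-zero prognostic correlation pushes the rate above nominal.

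Two stronger readings should be avoided. The fault is not simply a missing arm term, since adding one alone changes nothing. And the primary active-versus-sham comparison of CRS-R is not touched. This is a secondary analysis that should be corrected before the responder work is reported.

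**What to change.** In Secondary outcomes, replace the univariate regressions as the basis for any claim about predicting response to rTMS.

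1. **Parallel trial.** Regress outcome on marker, arm and marker-by-arm. Rest any such claim on the interaction. State that all randomized patients, sham included, enter the model.
2. **Classifier.** Include arm and its interactions with the EEG features.
3. **Crossover.** Use each patient's active-minus-sham CRS-R change at the same site as the outcome.
4. **Labelling.** Call a marker associated with outcome, but without an interaction, prognostic only.
5. **Status.** Report predictor findings as exploratory.

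**Cost.** Only the analysis wording changes, since the design already provides the sham sessions and the sham arm. The price is power: about 57% at N = 74 for r = 0.5 versus 0, and about 23% for 0.3 versus 0. Fewer markers will reach significance, and a null interaction will not show that a marker is not predictive.

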### Dissemination of results

Results of this clinical trial will be published in peer-reviewed open-access journals as original research articles and will be presented at various scientific conferences. The first publication will cover the clinical (CRS-R) and electrophysiological (connectivity markers) results of the RCT. The second publication is planned to report the clinical (CRS-R) and electrophysiological (connectivity markers and PCI) results of the personalized clinical trial and the follow-up period. A third publication is reserved for a detailed description of the machine-learning classifier developed to determine the features of treatment responders.

## Discussion

The current state of experimental science and medicine only offers few adequate therapeutic options for patients with prolonged and chronic DoC and their long-term management is becoming a public health concern (4). Moreover, the absence of clear consensus regarding a patients’ prognosis coupled with the lack of therapeutic opportunities may play a critical role in medical care decisions having an undeniable impact on patient’s survival. Because of these issues, it is crucial that more resources be put in place to further verify the potential effect of new therapies in robust settings and define who they might benefit to the most. In that context, some patients with DoC after severe brain injury can be successfully treated with non-invasive therapeutic interventions (7), among which rTMS seems to be the most effective option (25). However, there is currently a debate on whether recovery is mostly supported by the frontal or the posterior networks and structures (26, 58). While there seems to be evidence for the efficacy of targeting both regions with rTMS in promoting behavioral and/or electrophysiological recovery in patients with DoC (13, 17, 24, 59, 60), this protocol describes, to the authors’ knowledge, the first study investigating a direct comparison of the frontal versus parietal theories of stimulation hotspots (26). This clinical trial could help to understand which stimulation hotspot for non-invasive brain stimulation with rTMS is best suited for a patient. While the best research designs to support treatment efficacy in a given population are indisputably RCT, it becomes more and more evident that the field of therapeutic management of DoC patients is guided towards the direction of a personalized treatment approach instead of systematic randomization (61–63). Indeed, as described earlier, significant positive results are rarely observed in all DoC patients following non-pharmacological interventions. This suggests that not all patients can benefit from all types of interventions, thus supporting the clinical approach which pays particular attention to each patient characteristics and potential positive response to treatment in order to design a treatment plan. Thus, by positioning itself in that direction, this protocol acts as a major step in the pioneering approach of the development of patient-fitted tailored interventions. Although there is already existing evidence regarding certain endotype markers that may allow for response to brain stimulation treatments, the field is still at its debuts and needs massive joint efforts to provide conclusive guidelines for the clinical setting. In that sense, our personalized approach might help to increase the number of responders as compared to previous RCTs in the literature. Consequently, such increased number of responders will allow us to extract and define a possible phenotype regarding the effectiveness of transcranial magnetic brain stimulation.

The overall goal of this personalized trial is to improve the functional recovery at the clinical level. At the electrophysiological level, this study offers the opportunity to test different models of consciousness: anterior stimulation will allow to study the effect on consciousness recovery (32) according to the fronto-parietal mesocircuit model (28, 29) and the global neuronal workspace theory, suggesting that the hotspot of consciousness is located at the front of the brain (33, 34). Posterior stimulation – on the contrary – will allow for the testing of IIT claiming that the posterior part of the brain is the hotspot of consciousness (26, 27). We will use neurophysiological assessments as well as neurobehavioral exams to test the hypothesis that rTMS can modulate the neural network of the severely injured brain to promote the recovery of both consciousness at the clinical level, and functional thalamocortical network integrity at the neurobiological level. As such, this trial will bring direct evidence to challenge the above-mentioned models and will shed new light on the use of frontal and parietal rTMS as a therapeutic candidate to treat DoC.

A potential pitfall of this protocol might be the challenging timeframe of investigation. Indeed, full completion of the procedure of both trials should add-up to a total of 9 weeks. This is a particularly challenging feature since as we mentioned earlier, DoC patients are a very fragile population prone to complications and management issues. Safety precautions will be taken to avoid potential harm to the patients during the study, especially during the rTMS stimulation sessions, and to allow patients to complete the protocol.

This protocol stands as an important milestone in the development of new patient-tailored therapeutic options in the field of DoC. Our findings could usher in a new era of research for a challenging patient population in desperate need of medical solutions.

